### Blood Sample Collection and Storage

Venous blood samples will be collected by certified laboratory technicians. Participants will be instructed to maintain an 8 to 12 hours fast and to abstain from alcohol for at least 72 hours before sample collection. Blood will be drawn aseptically into the following tubes: 2 plain tubes, 3 ethylenediaminetetraacetic acid tubes, and 1 gray-top (fluoride) tube. Samples showing signs of hemolysis will be excluded from further analysis. The collected samples will be used for routine biochemical investigations, including complete blood count, glycated hemoglobin (HbA_1c_), liver function tests, kidney function tests, lipid profile, thyroid profile, fasting blood glucose, vitamin B12, and folate levels in serum. For metabolomic analysis, 1 plain and 1 ethylenediaminetetraacetic acid tube will be used, and the samples will be transported via cold chain. All samples will be centrifuged at 2500 rpm for 15 minutes at room temperature to separate serum and plasma within 1 hour of drawing the sample. The separated components will be aliquoted into cryovials and stored immediately at –80 °C until further analysis.

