### Randomization

Participants will be randomly assigned to the intervention or control group using a computer-generated list. As age is the most significant risk factor for cognitive decline, and our study has a relatively small sample size, we will do a stratified randomization by age (45‐60 and 61‐75 y) to avoid significant baseline differences pertaining to age in the 2 groups. The sequence will be created using Stata 17 by an independent statistician. Unique IDs starting with “BRY2001-BRY2038” for younger and “BRE3001-BRE3038” for older participants will be assigned prior to allocation to ensure a systematic and unbiased process. To maintain a 1:1 allocation ratio and minimize selection bias, a block size of 4 will be applied within each age stratum. This approach ensures that participants in both age groups are evenly distributed between the intervention and placebo arms. To prevent selection bias, the randomization list will be kept strictly confidential and accessible only to the independent statistician, who will not be involved in recruitment or data collection.

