### Follow-Up

There are 3 in-person primary data collection points in the study: “baseline evaluation (week 0),” “postintervention assessment at 12 weeks,” and “second follow-up assessment at 24 weeks.” Between the in-person visits, participants will receive weekly telephonic follow-up calls to promote participant retention, monitor medication adherence, and collect information on any SAEs. In the case of any SAEs, participants will be instructed to discontinue the study medication immediately and to contact the study team for appropriate medical evaluation. In such scenarios, unblinding will be done by the statistician who has access to the randomization and conveyed to the treating medical team. Following completion of the 12-week intervention period, participants will return to the hospital for a comprehensive follow-up visit, which will include assessment of primary and secondary outcome measures; and blood sample collection for postintervention metabolomic analysis, and repeat laboratory investigations, including hematological, hepatic, and renal function tests. Participants will be allowed to withdraw from the study if they wish to do so, and the reason for withdrawal will be clearly documented. They will be encouraged to return the used bottles at the end of 12 weeks or if they withdraw from the study at any time point, for pill count to confirm adherence. The second follow-up assessment will take place at 24 weeks and will include detailed cognitive evaluation. Blood sampling will not be done at this time point. Participants will continue to receive posttrial standard of care from their treating physicians.

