#### Planned Analyses

As mentioned previously, data will be entered into REDCap, a secure web-based application for managing databases. A data monitoring committee is not needed for this trial, as it is a short-duration study and the known risks of the intervention drug are minimal. No interim analysis is planned. Data will be analyzed using Stata version 17.0 (StataCorp LLC, College Station, TX, USA) and presented data as number (%), mean (SD), or median (IQR), as appropriate. Pearson chi-square test or Fisher exact test will be used (as appropriate) for qualitative variables. For quantitative variables, normality will be assessed using the Shapiro-Wilk test. The Student *t* test for independent samples will be used to compare differences in means for normally distributed quantitative variables. The Mann-Whitney *U* test will be used for quantitative variables with a distribution other than normal. All tests will be 2-tailed, and a *P* value <.05 will be considered statistically significant. Raw scores of each cognitive test will be converted to a *z* score (*z* score=[individual participant raw score – group mean]/group SD) for each participant. The group mean and SD will be derived by pooling the baseline scores of all participants. For all the tests, a higher *z* score will indicate better performance, except for the trail making tests A and B. The signs of these two tests will be inverted for a uniform interpretation. Both intention-to-treat and per protocol analysis will be done. Generalized linear mixed models with a between-subject factor of group (treatment vs placebo) and within-subject factor of time (baseline, mid-point, end point) will be conducted to assess differences in continuous primary and secondary outcome measures. Planned simple contrasts will be conducted to assess all time points (baseline vs. 12 wk, 12 wk vs. 24 wk, and baseline vs 24 wk). To handle any missing data, analysis of last observation carried forward will be undertaken within the intention-to-treat analysis model. Comprehensive statistical and functional analysis pertaining to the metabolomics will be performed using MetaboAnalyst version 6.0. The investigation based on observed peak values will encompass principal component analysis, partial least squares discriminant analysis, ANOVA, and molecular pathway identification. Heat maps will be developed with samples arranged in columns and features in rows, presented in a gradient from cold to hot. Pathway analysis will be conducted utilizing the integrated features of MetaboAnalyst 6.0, which includes the Kyoto Encyclopedia of Genes and Genomes and the Human Metabolome Database.

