### Baseline Characteristics

As of November 2025, a total of 60 participants had been recruited, with a mean age of 62.2 (SD 8.1) years. Most participants were men (53/60, 88.3%), and 47/60 (78.3%) had completed at least high school (Table 2). Among the risk factors, 39/60 (65%) had diabetes, 33/59 (55.9%) had dyslipidemia, 29/60 (48.3%) had hypertension, 29/60 (48.3%) were overweight or obese, 15/60 (25%) had coronary artery disease, and 13/60 (21%) reported a positive family history of dementia (Table 3). The biochemical profile and the cognitive raw scores are provided in Tables S3 and S4 in Multimedia Appendix 1, respectively.

**Table 2. T2:** Baseline sociodemographic characteristics of the participants.

Characteristics	Whole cohort (N=60)
Age, y, mean (SD)	62.2 (8.1)
Men, n (%)	53 (88.3)
Married, n (%)	57 (95)
Education (high school and above), n (%)	47 (78.3)
Occupation, n (%)	
Unemployed	3 (5)
Semiskilled and skilled workers	27 (45)
Semiprofessional to professional	16 (26.7)
Arithmetic skill job	14 (23.3)
Monthly family income (INR^a^), mean (SD)	37,462.5 (18,584.7)
Socioeconomic status, n (%)	
Upper class	37 (61.7)
Middle class to upper-middle class	20 (33.3)
Lower class to lower-middle class	3 (5)

a 1 INR equals US $0.011.

**Table 3. T3:** Baseline risk factor profile of the participants.

Characteristics	Whole cohort (N=60)
Height (cm), mean (SD)	163.7 (6.9)
Weight (kg), mean (SD)	68.4 (10.2)
Body mass index (kg/m²), mean (SD)	25.6 (3.8)
Average SBP^a^ (mm Hg), mean (SD)^b^	126.7 (16.5)
Average DBP^c^ (mm Hg), mean (SD)^b^	75 (10.5)
Pulse rate (bpm), mean (SD)	92.5 (11.8)
Duration of forgetfulness (months), mean (SD)	40.8 (23.6)
Hypertension, n (%)	29 (48.3)
Duration of hypertension (months), median (IQR)	72 (3-138)
Diabetes, n (%)	39 (65)
Duration of diabetes (months), median (IQR)	96 (36-186)
CAD^d^, n (%)	15 (25)
Duration of CAD (months), median (IQR)	120 (90-162)
Dyslipidemia, n/N (%)	33/59 (55.9)
Overweight, n (%)	20 (33.3)
Obese, n (%)	9 (15)
Hypothyroidism, n (%)	3 (5)
Hyperthyroidism, n (%)	5 (8.3)
Alcohol use, n (%)^e^	3 (5)
History of smoking, n (%)	0 (0)
Family history of dementia, n (%)	13 (21)

a SBP: systolic blood pressure.

b Average of 3 readings taken 2 minutes apart.

c DBP: diastolic blood pressure.

d CAD: coronary artery disease.

e Not fulfilling the National Institute on Alcohol Abuse and Alcoholism criteria of alcohol abuse.

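### The metabolite comparison is planned as plain ANOVA without baseline, age-stratum or diabetes adjustment; a covariate-adjusted between-arm model would gain precision at no cost

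*Protocol article*

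**What the plan says.** Planned Analyses in the protocol article describes the metabolite analysis in one sentence: "The investigation based on observed peak values will encompass principal component analysis, partial least squares discriminant analysis, ANOVA, and molecular pathway identification". It names MetaboAnalyst 6.0 as the software. It names no covariate and does not say which groups or visits the ANOVA compares. The model for continuous outcomes in the same section is likewise limited to group and time: "Generalized linear mixed models with a between-subject factor of group (treatment vs placebo) and within-subject factor of time".

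Other sections give the context:

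- **Sampling.** The Abstract places metabolomic profiling at weeks 0 and 12, so every completer has a baseline value.
- **Randomization.** Age is the only stratification factor: "we will do a stratified randomization by age". Blocks of four are used within each age stratum.
- **Baseline Characteristics.** "Among the risk factors, 39/60 (65%) had diabetes, 33/59 (55.9%) had dyslipidemia".
- **Blood Sample Collection and Storage.** The routine panel is listed as "including complete blood count, glycated hemoglobin (HbA_1c_), liver function tests, kidney function tests, lipid profile, thyroid profile, fasting blood glucose", with no visit attached. Samples are fasting.
- **Follow-Up.** The week 12 visit has "repeat laboratory investigations, including hematological, hepatic, and renal function tests".
- **Intervention Arm.** Drugs for comorbidities are allowed, and changes to them are recorded.

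**The concern.** Diabetes is present in about two thirds of the sample. It is not a stratification factor, and the metabolite analysis does not adjust for it. The Introduction and Discussion motivate the metabolomics with amino-acid, energy and lipid pathways. If levels in those pathways differ between people with and without diabetes, diabetes adds between-person noise that the analysis does not remove, and an uneven split between arms moves the observed difference.

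The same holds more generally. The week 0 value of each metabolite and the age stratum are known for every participant and are not used as covariates. The trial is small, and Strengths and Limitations already concedes insufficient power for efficacy. What is at stake is how much the secondary outcome on metabolites and pathways can show.

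**Working it through.** **The plan's own figures.** None is given for the metabolomic outcome. The sample sizes reproduce: a 0.5 SD difference at two-sided 5% and 80% power needs 64 per arm (noncentral t); 128/0.8 = 160; 30/0.8 = 37.5, rounded up to 38 per arm, or 76. The prevalences also reproduce: 39/60 = 65.0% and 33/59 = 55.9%.

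**Step 1: chance imbalance in diabetes.** Inputs are 65% prevalence (Baseline Characteristics) and 30 or 38 per arm (Sample Size Estimation). Two calculations were made, both ignoring the age strata and blocks.

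(a) Two independent binomial arms with p = 0.65.

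(b) Fixed totals. Diabetics in one arm follow a hypergeometric distribution with 39 of 60, or with 49 of 76 (0.65 × 76 = 49.4, assuming the rate holds). If x of K diabetics fall in one arm of size n, the gap is |2x − K|/n.

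| Per arm | Gap | (a) binomial | (b) fixed totals |
|---|---|---|---|
| 30 | at least 10 points | 0.499 | 0.589 |
| 30 | at least 20 points | 0.136 | 0.103 |
| 38 | at least 10 points | 0.400 | 0.338 |
| 38 | at least 20 points | 0.071 | 0.054 |

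Under (b) the gap moves in steps. At 30 per arm a gap of 3/30 = 10.0 points just counts. At 38 per arm 3/38 = 7.9 points does not, and the next step is 5/38 = 13.2 points. The SD of the gap at 30 per arm is 2 × √(30 × 0.65 × 0.35 × 30/59)/30 = 0.124, or 12.4 points.

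**Step 2: does omitting diabetes bias a between-arm test?** Simulation of an unadjusted t test with 30 per arm, 39 diabetics allocated at random, no treatment effect and 20,000 runs gave type I error of 4.9%, 5.1% and 4.9% when diabetics differ by D = 0, 1 and 2 SD. It does not: averaged over randomization, the test keeps its level.

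**Step 3: given a realised 20-point gap.** The shift is 0.2D and the standard error is √[(2/30)(1 + 0.65 × 0.35 × D²)].

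- D = 0.5: 0.10/0.265 = 0.38 standard errors; conditional error about 7%.
- D = 1: 0.20/0.286 = 0.70 standard errors; conditional error about 11%.

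With a 10-point gap the corresponding errors are about 5% and 6%. Here D is the difference on whatever quantity is compared. A stable difference in level cancels if change from baseline is compared.

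**Step 4: precision.** Diabetes carries a share 0.2275D²/(1 + 0.2275D²) of the variance, where 0.2275 = 0.65 × 0.35. This is 0.0569/1.0569 = 5.4% at D = 0.5 and 0.2275/1.2275 = 18.5% at D = 1. Adjusting for the week 0 level multiplies the variance of the week 12 comparison by about 1 − ρ², where ρ is the correlation between visits. The article gives no ρ, so this gain is not quantified.

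The values of D are assumptions; the article gives no metabolite difference by diabetes status.

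**The case against.** The strongest reply is that this is a randomized, double-blind, placebo-controlled trial. Diabetes and its background treatment are balanced in expectation, and the standard error already allows for chance imbalance. Covariates for an exploratory omics outcome are also commonly left to an analysis plan, which is not shown. All of this stands. The point is therefore an improvement on the method stated, not an error or an omission. It survives because the article does name the method, and a better one uses data already collected.

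A reader might infer more, and the documents do not support it:

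- **That diabetes-related shifts cannot be told apart from a Bacopa effect.** For a between-arm comparison step 2 shows otherwise. The risk would be real for a pre-post test within the Bacopa arm alone: if diabetics drift by 0.3, 0.5 or 0.8 SD of change with no drug effect (assumed, n = 30), such a test is falsely significant in about 18%, 39% or 73% of cases. The article does not commit to that contrast. It leaves the contrast unstated, which is a reason to state it.
- **That the assay targets amino-acid pathways.** It is untargeted, and Objectives and Outcomes speak of metabolites and pathways generally. Amino acids are rationale.
- **That glycaemia is not measured at week 12.** The Follow-Up list is introduced as non-exhaustive, and the general panel, which includes HbA1c and fasting glucose, is not tied to one visit.
- **That participants whose prescriptions change should be dropped from the main comparison.** Such changes arise after randomization, and conditioning on them could introduce bias if Bacopa affects glycaemia or lipids.

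**Conclusion.** The point holds as a matter of efficiency. The stated metabolite analysis uses neither the baseline level, nor the stratification factor, nor a common baseline condition as a covariate. At 30 to 38 per arm, a diabetes gap of at least 10 points is common (34-59% across both calculations) and one of at least 20 points is uncommon but not rare (5-14%). The consequence of a 20-point gap is modest: a conditional error of about 7% to 11% if diabetes shifts the compared quantity by 0.5 to 1 SD. The variance that adjustment for diabetes could remove is about 5% to 19% under the same assumption.

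These sizes rest on the 65% rate holding to full recruitment, on ignoring the age strata and blocks, and on assumed diabetes effects. There is no systematic bias in a between-arm comparison. The outcome is secondary and exploratory, and the primary memory outcome is untouched.

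**What to change.** In Planned Analyses, replace plain ANOVA with a linear model for each metabolite. Compare Bacopa with placebo on change from week 0 to week 12, or on the week 12 level adjusted for the week 0 level. Include age stratum and baseline diabetes status (or baseline HbA1c) as covariates. Stating this between-arm contrast also rules out a pre-post reading within one arm. PCA, PLS-DA and the pathway step can stay as described.

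Report documented prescription changes, and any week 12 glycaemic results, by arm as description or in a labelled sensitivity analysis. Do not use them as covariates or exclusions in the main comparison.

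The cost is analysis wording and a short regression script. Stata 17 is already named for the other outcomes, the covariates are collected at baseline, and no extra assay or visit is needed. Data collection is due to end in June 2026 and analysis to begin after that, so the model can be fixed before analysis starts.

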## Results

### Study Status and Timeline

The study was funded in October 2023, and the first participant was enrolled in April 2024. Data collection will conclude in June 2026, after which data analysis will begin and be completed by September 2026, with primary findings targeted for publication in spring 2027.

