### Statistical Methods

#### Sample Size Estimation

There are no previous studies investigating the effects of *B. monnieri* versus placebo in patients with aMCI, looking at changes in composite memory *z* scores as the primary outcome. By considering a clinically relevant effect size as a SD change of 0.5, a 2-sided α at 5%, and 80% power, a sample size of 128 (64 in each group) was calculated. With a 20% dropout rate, the final sample size reached 160 (80 in each group), which did not seem feasible for the selected patient population in the specified duration. Therefore, a sample size of 60 (30 in each group) is determined for this exploratory study based on feasibility. The sample size was further adjusted for a dropout rate of 20% and 76 participants (38 in each group) will be recruited for this study.

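### At the average accrual reported in the article, closing data collection in June 2026 leaves about 8–12 of the planned 76 participants without a week-24 visit

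*Protocol article*

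**What the plan says.** Sample Size Estimation sets the target: "76 participants (38 in each group) will be recruited for this study". That is a feasibility figure of 60 raised for dropout.

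Follow-Up gives every participant a last in-person visit: "The second follow-up assessment will take place at 24 weeks and will include detailed cognitive evaluation". Under Outcomes, week 24 carries secondary endpoints: the memory z score, the other cognitive domains, and the proportion with meaningful improvement. The primary outcome is memory at week 12.

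On progress, Study Status and Timeline says "the first participant was enrolled in April 2024", and Baseline Characteristics says "As of November 2025, a total of 60 participants had been recruited". On closure, Study Status and Timeline says "Data collection will conclude in June 2026, after which data analysis will begin and be completed by September 2026", with publication aimed at spring 2027. The Abstract repeats these dates.

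Planned Analyses handles missing data in the intention-to-treat analysis by last observation carried forward (LOCF). It makes no exception for visits that were never reached.

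**The concern.** The last participant's week-24 visit comes 24 weeks after enrolment, so a June 2026 close implies an enrolment deadline around the turn of the year. In November 2025 sixteen people were still to be recruited, and the average pace to that point is too slow to find them by then.

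If the dates are followed as written at that pace, some late enrollees would have no week-24 data for purely administrative reasons, on top of the 20% dropout allowed for. The LOCF rule would then put their end-of-treatment week-12 score in place of a score taken 12 weeks after treatment stopped. That fixes their 12-to-24-week change at zero. The week-24 visit exists to show whether any effect lasts (Strengths and Limitations), so the imputation would assume the answer for those people. Two of the three planned time contrasts use week 24.

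**Working it through.** **The plan's own sample size first.** The formal calculation uses "a clinically relevant effect size as a SD change of 0.5, a 2-sided α at 5%, and 80% power".

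- Normal approximation: n per arm = 2 × (1.960 + 0.842)² / 0.5² = 62.8, so 63. The t-test solution is 63.8, so 64 per arm and 128 in total, as stated.
- Dropout: 128 / 0.8 = 160, as stated.
- Feasibility size: 30 / 0.8 = 37.5, so 38 per arm and 76 in total, as stated.

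The target of 76 reproduces. The difficulty lies only in the calendar.

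**Inputs for the calendar.** The article gives months without days, so each was varied: first enrolment 1–30 April 2024, the count of 60 on 1–30 November 2025, and the close 1–30 June 2026. Week 12 is 84 days, week 24 is 168 days, and a month is 30.4375 days.

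**Accrual rate** = 60 / (count date − first enrolment date).

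- Slowest: 1 April 2024 to 30 November 2025 is 608 days; 60 / 608 × 30.4375 = 3.00 a month.
- Fastest: 30 April 2024 to 1 November 2025 is 550 days; 60 / 550 × 30.4375 = 3.32 a month.

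**Numbers able to reach week 24.** The last useful enrolment date is the close minus 168 days; for 30 June 2026 that is 13 January 2026. Enrolled by then = 60 + daily rate × days from the count date.

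- Slowest: 60 + (60/608) × 44 = 64.3, which is 11.7 short of 76.
- Fastest: 60 + (60/550) × 73 = 68.0, which is 8.0 short.

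**Rate needed to enrol the last 16 in time.**

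- From 30 November: 16 / 44 × 30.4375 = 11.1 a month, 3.7 times the slowest average.
- From 1 November: 16 / 73 × 30.4375 = 6.7 a month, 2.0 times the fastest average.

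**Over the possible June dates:**

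| Close | Last enrolment for week 24 | Enrolled by then | Short at week 24 | Rate needed ÷ average | Last enrolment for week 12 | Short at week 12 |
|---|---|---|---|---|---|---|
| 30 June | 13 Jan 2026 | 64.3–68.0 | 8.0–11.7 | 2.0–3.7 | 7 Apr 2026 | 0–3.4 |
| 15 June | 29 Dec 2025 | 62.9–66.3 | 9.7–13.1 | 2.5–5.6 | 23 Mar 2026 | 0.5–4.8 |
| 1 June | 15 Dec 2025 | 61.5–64.8 | 11.2–14.5 | 3.3–10.8 | 9 Mar 2026 | 2.0–6.2 |

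**When the trial would finish at the average pace.** The remaining 16 take 16 / 3.32 = 4.8 to 16 / 3.00 = 5.3 months. The 76th participant enrols between about 27 March and 11 May 2026. Adding 168 days puts the last week-24 visit between about 11 September and 26 October 2026. That is 73 to 118 days after 30 June, or roughly 2.5–4 months, and falls in or after the month in which analysis is due to be complete.

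**Numbers left after dropout.** If 64–68 can reach week 24 and 20% drop out, about 51–54 remain (64 × 0.8 = 51.2; 68 × 0.8 = 54.4). The feasibility size was 60.

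**The case against.** The strongest reply is that this is a forecast. No stated figure is miscalculated, and the conflict appears only if the average accrual continues. The article gives one cumulative count, with no monthly series or screening pipeline, so the pace in late 2025 may have been faster or slower than the average. This stands. A reader might infer that 76 participants and a June close cannot both hold, but the documents do not support that: they can, if sixteen people enrol by mid-January.

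A reader might also infer that the trial must either fall short of 76 or lose week-24 data. That does not follow either. Nothing makes June 2026 a hard cut-off, and the closing date may simply slip. The LOCF consequence arises only if accrual stays at its average, enrolment continues towards 76, the close is held, and the rule is applied to visits cut off by it. What remains is that the rule as written covers any missing data, and the article mentions no faster recruitment, lower target or waiver of week 24 for late enrollees.

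Finally, the size carries limited inferential weight. The article says "a sample size of 60 (30 in each group) is determined for this exploratory study based on feasibility" and concedes under Strengths and Limitations that power is insufficient. So 64–68 at week 24 falsifies no power claim. Actual dropout is not reported, so the 51–54 above is only illustrative.

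**Conclusion.** The point holds as a conditional one. If accrual continues at the reported average of 3.0–3.3 a month, a June 2026 close does not fit 76 participants with a 24-week visit. On the most lenient reading (30 June), about 64–68 can reach week 24, 8–12 short; with a 1 June close the shortfall is 11–14.5. No reading of the months removes the gap at that pace.

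It would be wrong to read this as a threat to the primary outcome. At week 12 the shortfall is 0 to about 3 with a 30 June close, and up to about 6 with 1 June. The effect falls mainly on the 24-week secondary outcomes and on how their missing values are filled.

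The result rests on constant accrual, a visit exactly 24 weeks after enrolment with no visit window, and a close that is actually enforced.

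**What to change.** - Define the end of data collection as the last enrolled participant's week-24 visit, about mid-September to late October 2026 at the reported accrual, and move the analysis dates to match. Allowing the same roughly three months for analysis, it would end between about mid-December 2026 and late January 2027, still before spring 2027.
- If June 2026 is fixed, state the number expected to have week-24 data: about 64–68 before dropout with a 30 June close, fewer with an earlier one.
- In either case, state before unblinding that week-24 visits not reached because of the close are administratively missing. Leave them missing in the planned mixed model, which can use the participants' earlier visits, and do not carry week-12 scores forward.

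The cost is an analysis date roughly 2.5–4 months later, or a slightly smaller stated size at week 24. No new procedures or visits are needed.
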